### Objectives {7}

The current study will expand on previous evaluations of BRIDGE by conducting a randomized controlled trial (RCT) comparing (1) BRIDGE (DBT skills training + Parenting Skills), (2) DBT (DBT skills training only), and (3) services as usual (SAU). Our primary aim is to examine the effects of BRIDGE on maternal depression and child MI symptoms. We hypothesize that participants who receive the BRIDGE and DBT interventions will report fewer depressive symptoms than participants in the SAU group. Participants who receive the BRIDGE intervention are hypothesized to report fewer child MI symptoms than those in the DBT and SAU groups. Our secondary aim is to evaluate the efficacy of BRIDGE in reducing parenting stress and harsh parenting. Participants who receive the BRIDGE intervention are hypothesized to show lower levels of parenting stress and harsh parenting than those in the DBT and SAU groups.

Additional aims of the RCT are to examine the effects of BRIDGE and DBT on family relationships, other service use (e.g., hospital visits, interactions with police), and maternal psychopathology symptoms. We hypothesize that mothers who receive the BRIDGE or DBT intervention will report lower psychopathology symptoms, reduced service use, and improved family relationship quality. We will also assess participants' engagement in each intervention.

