### Sample size {14}

A sample size of 180 participants will be sufficient to assess clinically meaningful reductions in both maternal depressive and child MI symptoms between groups. Based on the feasibility pilot data, we assume an effect size of *d* = 1.02 in improvement on maternal depression symptoms for both intervention groups (BRIDGE and DBT Skills-Only) [36]. A sample size of *n* = 60 per group will provide very high power (> 99%) to compare intervention groups to SAU. Based on pilot data on child MI symptoms, we assume a within-group SD of 13 on the CBCL and a mean improvement of 14 points [36]. As we anticipate little to no improvement in the SAU arm, we assume an effect size of* d* = 1.08 between BRIDGE and SAU and an effect size of *d* = 0.54 between BRIDGE and DBT-Only (i.e., an effect size 50% smaller than for BRIDGE, based on meta-analyses on the benefit of dual generation programs) [27]. A sample size of *n* = 60 per group will provide very high power (> 99%) to compare BRIDGE with SAU and adequate power (75%) to compare BRIDGE with DBT Skills-only.

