## Statistical methods

### Statistical methods for primary and secondary outcomes {20a}

Analyses for primary and secondary outcome variables, as well as exploratory outcome variables, will compare the changes over time between (a) the BRIDGE vs SAU groups and (b) BRIDGE vs DBT-only groups, each at *a* = 0.025 (combined type I error rate to 0.05). Linear models accounting for pre-intervention scores will be used as the primary analysis method. The persistence of effects at the 6-month follow-up will be examined using time-by-intervention interactions in a linear mixed-effects model, accounting for within-subject serial correlations and between-subject effects of the intervention and covariates. Standardized effect sizes for linear mixed models will be derived based on recommendations for linear mixed models [70, 71]. Standardized effect sizes of 0.20, 0.50, and 0.80 will be used to interpret small, medium, and large effects, respectively [70]. The research team will also investigate if there is baseline moderation by symptom severity to examine whether the BRIDGE intervention is more effective than the DBT-only or SAU interventions for participants who have higher symptom levels at pre-intervention.

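### The fixed 0.025 split between the two BRIDGE contrasts is valid but gives up power: on the plan's own child-symptom inputs, Holm at the same 0.05 per outcome raises BRIDGE vs DBT-only from 75% to about 83.5%

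*Protocol article*

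**What the plan says.** The section on statistical methods for primary and secondary outcomes {20a} names two contrasts for every outcome, BRIDGE against SAU and BRIDGE against DBT-only. On the significance level its wording is "each at *a* = 0.025 (combined type I error rate to 0.05"). It gives no order of testing and no rule for reusing alpha once one contrast succeeds. Sidedness is not stated.

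The sample size section {14} sets the child-symptom inputs: "we assume a within-group SD of 13 on the CBCL and a mean improvement of 14 points". The standardised effect against SAU is set at d = 1.08. For the other contrast the plan assumes "an effect size of *d* = 0.54 between BRIDGE and DBT-Only". With 60 per group it claims "very high power (> 99%) to compare BRIDGE with SAU and adequate power (75%) to compare BRIDGE with DBT Skills-only".

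The objectives {7} state the child hypothesis against both comparators: "Participants who receive the BRIDGE intervention are hypothesized to report fewer child MI symptoms than those in the DBT and SAU groups". Parenting stress and harsh parenting are also hypothesised to be lower under BRIDGE than in both other arms.

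**The concern.** On the child outcome the plan treats BRIDGE vs SAU as nearly certain to succeed, yet permanently sets aside half the alpha for it. Once that test rejects, its 0.025 is spent and the other contrast cannot use it. BRIDGE vs DBT-only, which shows whether the parenting content adds anything, stays at 0.025 and carries the lowest power that the plan states.

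In practice, suppose BRIDGE vs SAU is overwhelming and BRIDGE vs DBT-only gives p = 0.03. The protocol's rule calls the second contrast negative. A step-down rule with the same 0.05 guarantee for that outcome would call it positive.

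**Working it through.** **Inputs.** From the sample size section: n = 60 per group; CBCL SD 13 and improvement 14, so 14/13 = 1.077, taken as d = 1.08 against SAU; half of that, d = 0.54, against DBT-only. From the statistical methods section: alpha 0.025 per contrast, 0.05 combined. Two-sided testing is an assumption, checked in step 1.

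**Step 1: reproduce the plan's figures.** For a two-sample t-test, the noncentrality is d × √(n/2) with 2n − 2 = 118 degrees of freedom.

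- BRIDGE vs DBT-only: 0.54 × √30 = 2.958. At two-sided 0.025 the noncentral-t power is 75.3% (normal approximation: Φ(2.958 − 2.241) = 76.3%). This is the stated 75%.
- BRIDGE vs SAU: 1.08 × √30 = 5.915. At two-sided 0.025 the power is 99.98%, matching >99%.
- Two-sided 0.05 and one-sided 0.025 both give 83.5% for BRIDGE vs DBT-only. So among the readings tried, two-sided 0.025 fits: the 75% was computed under the fixed split.

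**Step 2: why Holm dominates.** Holm tests the smaller p-value at 0.025 and, if it is significant, the other at 0.05. Any p-value below 0.025 is rejected under both rules. Holm adds a rejection only when one p-value is below 0.025 and the other lies between 0.025 and 0.05. It therefore never rejects less than the split, and it holds family-wise error at 0.05 whatever the dependence between the tests.

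**Step 3: size of the gain.** BRIDGE vs DBT-only is rejected under Holm if its p < 0.025, or if its p < 0.05 and BRIDGE vs SAU has p < 0.025. As the latter has probability 99.98%, Holm power is practically the power at 0.05: 83.5% by noncentral t (normal approximation Φ(2.958 − 1.960) = 84.1%). A simulation of three arms sharing the BRIDGE arm (400,000 replicates) gave 75.2% for the split and 83.5% for Holm. The chance of missing the planned effect falls from about 25% to about 16.5%. Reaching 80% under the split would take 67 per group, or 3 × 7 = 21 more participants.

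**Step 4: dependence on the inputs.** Power for BRIDGE vs DBT-only with 60 per arm, by simulation; all rows but the first use assumed effects:

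| d vs SAU | d vs DBT-only | Split | Holm | Fixed sequence, SAU first |
|---|---|---|---|---|
| 1.08 | 0.54 | 75.2% | 83.5% | 83.5% |
| 0.80 | 0.54 | 75.3% | 83.3% | 83.2% |
| 0.54 | 0.54 | 75.4% | 80.5% | 73.7% |
| 0.30 | 0.54 | 75.4% | 76.3% | 35.2% |
| 0.41 | 0.205 | 13.0% | 17.8% | 17.1% |
| 0.39 | 0.39 | 45% | 50% | 40% |

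The sample size section makes no allowance for dropout. If retention matched the pilots (86% and 92.3%, an assumption), 60 × 0.86 ≈ 52 and 60 × 0.923 ≈ 55 per arm would be analysed. Power would be 68% and 71% under the split, against 78% and 80% under Holm.

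**Step 5: error rates.** With no true differences, family-wise error is 4.6% under both rules, because Holm's first step is the split. When BRIDGE equals DBT-only and both clearly beat SAU, the false-positive rate for BRIDGE vs DBT-only is 2.5% under the split and 5.0% under Holm.

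**The case against.** The strongest reply is that nothing here is wrong. The split is valid, the power statement uses the same rule, and the plan openly calls 75% adequate. That stands. A reader might infer from the heading that type I error is mishandled or that the 75% is miscalculated; the documents support neither. The point is efficiency only, though the protocol does fix the rule rather than leave it to an analysis plan.

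Second, a sponsor may prefer the stricter 0.025 for the claim that parenting content adds benefit, since Holm can double the false-positive rate on that contrast. This stands as a cost to disclose. Family-wise error is unchanged at 0.05.

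Third, the 8-point gain relies on d = 1.08 against SAU, from the in-person pilot. The telehealth pilot, closer to this trial's delivery, gave a within-group d of 0.41 for child symptoms. With 0.41 against SAU and half that against DBT-only (an assumption), Holm gains about 5 points and the comparison remains badly underpowered. Holm is still better there, but it does not rescue the contrast.

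Fourth, one might treat a fixed sequence starting with SAU as interchangeable with Holm. It is not: it falls below the split when BRIDGE vs SAU is less than near-certain, as the table shows. No power is stated for the secondary outcomes, so that near-certainty cannot be presumed for them.

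Finally, it is tempting to call this the weakest comparison in the plan. The documents do not support that. The plan assumes d = 1.02 on depression for both BRIDGE and DBT-only, which implies no difference between them on that outcome, and the secondary outcomes have no stated power. It is the lowest power the plan states.

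**Conclusion.** The concern holds as a loss of efficiency, not as an error in type I control. On the plan's own child-symptom inputs, taken as two-sided, the fixed split yields 75% power for BRIDGE vs DBT-only where Holm yields about 83.5% at the same per-outcome 0.05, with no added participants. The size of the gain rests on a large BRIDGE vs SAU effect: it shrinks as that effect shrinks, but never becomes a loss. These figures come from an unadjusted t-test, the calculation that reproduces the plan's 75%; the planned adjustment for baseline scores would alter both.

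A reader might also infer that Holm settles multiplicity across the two primary outcomes. It does not. Both the split and Holm as described here work within one outcome at 0.05.

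**What to change.** In the statistical methods section {20a}, for the CBCL, parenting stress and harsh parenting, replace the fixed 0.025 per contrast with Holm at two-sided 0.05 per outcome: test the smaller of the two p-values at 0.025 and, if it is significant, the other at 0.05. Do not list a fixed sequence as an equivalent. In the sample size section {14}, restate BRIDGE vs DBT-only power as about 83–84% on its existing inputs.

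Make the change by documented amendment before any comparative results are seen. The protocol plans an interim analysis of primary and secondary outcomes at about 90 post-intervention completers, and its trial status section reports 78 participants randomised with post-intervention assessments under way. Relaxing a threshold after that look would invite the charge that the results drove it.

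The cost is one sentence of analysis wording and one power figure, with no change to participants, data or conduct. State two downsides: the false-positive rate for BRIDGE vs DBT-only rises from 2.5% to at most 5% when BRIDGE truly beats SAU, with family-wise error still at 0.05; and simultaneous confidence intervals that match Holm are less simple. Ordinary 97.5% intervals can still be reported alongside.

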### Outcomes {12}

#### Primary outcomes (the specific measures utilized are described below in data collection and management)

The primary outcome of this study is mean change in depressive symptoms in mothers from pre- to post-intervention as measured by a self-report questionnaire [39]. Another primary outcome of this study is mean change in child behavioral problems from pre- to post-intervention, measured by parent-report questionnaire [47].

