### Assignment of interventions: allocation

#### Sequence generation {16a}

Participants will be randomly allocated in a 1:1:1 ratio to the BRIDGE intervention, DBT-Skills intervention, or SAU. Stratified randomization will be applied based on (a) participants’ availability for virtual therapy timeslots (i.e., lunchtime or evening group) and (b) province of residence. Randomization will occur in blocks to ensure approximately equivalent group sizes.

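### The stated combined type I error of 0.05 holds within one outcome only; the plan has two primary outcomes and no rule linking them, so error across both can reach about 9%

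*Protocol article*

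**What the plan says.** The Objectives section {7} joins two targets in one primary aim: "Our primary aim is to examine the effects of BRIDGE on maternal depression and child MI symptoms". The Outcomes section {12} then names two primary outcomes. The first: "The primary outcome of this study is mean change in depressive symptoms in mothers from pre- to post-intervention". The second: "Another primary outcome of this study is mean change in child behavioral problems from pre- to post-intervention".

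The section on statistical methods for primary and secondary outcomes {20a} sets one testing rule for all variables: "Analyses for primary and secondary outcome variables, as well as exploratory outcome variables, will compare the changes over time". The comparisons are "a) the BRIDGE vs SAU groups and (b) BRIDGE vs DBT-only groups, each at" a level of "0.025 (combined type I error rate to 0.05").

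The hypotheses in {7} differ by outcome. For depression, BRIDGE and DBT are each expected to do better than SAU; no difference between BRIDGE and DBT is hypothesised. For child symptoms, BRIDGE is expected to do better than both DBT and SAU.

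**The concern.** The alpha is divided across the two arm comparisons and not across the two primary outcomes. Each primary outcome therefore uses a full 0.05, and a reader who takes the stated combined rate as covering the trial's primary results would be misled. Nothing in the article says that both outcomes must succeed, that one is tested first, or that the two are separate claims each held at 5%.

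If a result on either outcome may be reported as a positive primary finding, chance alone produces one more often than the printed 0.05 suggests. It also leaves open which primary result is given prominence once the data are seen.

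**Working it through.** **Inputs.** Level 0.025 per comparison, combined 0.05, two comparisons per outcome ({20a}). Two primary outcomes ({12}). Equal allocation: "Participants will be randomly allocated in a 1:1:1 ratio to the BRIDGE intervention, DBT-Skills intervention, or SAU" ({16a}). Sixty per arm; CBCL effect sizes d = 1.08 against SAU and 0.54 against DBT-only; PHQ-9 d = 1.02; stated power 75% for BRIDGE versus DBT-only ({14}). The correlation r between the two outcomes is not given, so it is varied as an assumption.

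**1. The plan's own figure.** One outcome, two tests: 2 × 0.025 = 0.05, as stated. Because both comparisons use the BRIDGE arm and arms are equal, their test statistics correlate at 0.5; simulation then gives 4.65%.

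**2. The alpha behind the sample size.** Two-sided t test, d = 0.54, n = 60 per arm:
- at 0.05: 83.5%
- at 0.025: 75.3%, matching the stated 75%
- at 0.0125: 66.3%

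So the sample size allowed for two comparisons but not for two primary outcomes.

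**3. Both primary outcomes.** Four tests at 0.025:
- Bonferroni bound: 4 × 0.025 = 0.10
- if independent: 1 − 0.975⁴ = 0.0963
- with the shared arm, simulated with no effect on either outcome (two-sided critical value 2.241):

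| r between outcomes | four tests | three hypothesised tests |
|---|---|---|
| 0 | 9.1% | 7.0% |
| 0.3 | 8.9% | 6.9% |
| 0.5 | 8.5% | 6.7% |
| 0.7 | 7.9% | 6.4% |
| 0.9 | 6.6–6.7% | 5.7% |

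The three hypothesised tests are PHQ-9 BRIDGE versus SAU and the two CBCL comparisons. The four-test figure returns to 4.65% only at r = 1.

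**4. If BRIDGE truly beats SAU on both outcomes.** Only the two BRIDGE versus DBT-only tests can then be false positives, and the bound is 2 × 0.025 = 0.05 (4.9% at r = 0, 4.6% at r = 0.5).

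**5. What a fixed order would cost.** The first test in each sequence acts as a gate at 0.025. With n = 60 per arm:
- CBCL gate at d = 1.08: power 99.98%
- PHQ-9 gate at d = 1.02: power 99.95%
- CBCL gate at d = 0.41, the pre-post effect that the Background {6a} reports from the telehealth pilot, applied here as a between-arm effect by assumption: power 49%

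In that last case, assuming half the effect against DBT-only (d = 0.205), BRIDGE versus DBT-only has about 13% power without the gate and about 11% with it.

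**The case against.** The strongest reply is that the parenthesis in {20a} refers only to comparisons (a) and (b), so that 0.05 is meant per outcome. The sentence covers primary, secondary and exploratory variables together, and no trial-wide 5% could hold over so many scales. On that reading the arithmetic is exact. This stands, and it rules out the stronger inference that the article makes a plainly false claim of 5% across outcomes. What remains is that the per-outcome meaning is not written, while the primary family is defined as two outcomes.

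A reader might also infer that the true error is simply 9% instead of 5%. The documents do not support that as a flat statement. It needs no effect on either outcome, low to moderate correlation between them, and all four tests counted, although {7} states no superiority hypothesis for BRIDGE over DBT on depression.

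Adjusting across two distinct primary questions is partly a matter of choice, and treating them as separate claims at 5% each is legitimate if declared. The Dissemination section {31a} mentions superiority on maternal and child outcomes together, but as a trigger for seeking scale-up funding and not as a success rule.

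Finally, a hierarchy is often left to the analysis plan, which is not shown. That would answer a complaint about a missing rule. It does not settle what the combined rate printed in the article covers.

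**Conclusion.** The point holds in limited form. The combined 0.05 is correct within one outcome and does not cover the two primary outcomes together. Across the four primary tests the bound is 0.10. With no effect on either outcome, family-wise error is about 9.1% to 6.6% for r from 0 to 0.9, or about 7.0% to 5.7% for the three tests with a stated superiority hypothesis; every value exceeds 5%. These figures assume that success on either outcome counts as a primary finding, and r is an assumption throughout. If BRIDGE does beat SAU on both outcomes, the remaining error is within 5%. Data collection is unaffected and the text is easily corrected, so this is a should-fix and not a must-fix.

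**What to change.** Rewrite the testing rule in {20a} in one of two ways.

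**Control across both outcomes.** Allocate 0.025 to the PHQ-9 and 0.025 to the CBCL, and test in fixed order within each, the second test only if the first succeeds:
- CBCL: BRIDGE versus SAU, then BRIDGE versus DBT-only
- PHQ-9: BRIDGE versus SAU, then DBT-only versus SAU

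Each sequence is held at 0.025, so the total is 0.025 + 0.025 = 0.05. State openly that DBT-only versus SAU is added to the comparisons in {20a} to match the depression hypothesis in {7}. State also that PHQ-9 BRIDGE versus DBT-only and all secondary and exploratory p-values are nominal.

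**Control per outcome.** If that is what is intended, say that 0.05 applies to each primary outcome separately and that the error across both can reach about 9%.

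**Cost.** One paragraph and no extra participants. With the fixed order, the second test is lost if the first fails. That is under 1% at the plan's d = 1.08 and 1.02, so the 75% for BRIDGE versus DBT-only on the CBCL is essentially kept; a plain split to 0.0125 per test would lower it to 66%. If d = 0.41 applied, the CBCL gate would fail about half the time, but BRIDGE versus DBT-only would then have little power in any case.

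The choice should be fixed before outcome data are analysed, including the interim analysis of primary outcomes planned in {21b}.

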#### Intervention description {11a}

##### BRIDGE condition

The BRIDGE program is a manualized therapy that provides participants with parenting and DBT skills video training modules through a secure website. Mothers in the BRIDGE arm will participate in 16 weeks of 20–30 min DBT and parenting skills training videos that will be delivered asynchronously via an online website requiring a participant login. The BRIDGE condition also includes weekly synchronous 1-h virtual group therapy sessions as well as DBT and parenting skills worksheets to complete weekly. Based on participant feedback from earlier iterations of BRIDGE, participants will not be asked to complete DBT Skills Diary Cards [36].

*DBT videos* developed and recorded by our research team will provide information to participants with the goal of targeting mental health symptomatology. Video content was drawn from concepts outlined in the DBT Skills Training Manual 2nd Edition [41]. Videos will provide training skills in Mindfulness, Emotion Regulation, Distress Tolerance, and Interpersonal Effectiveness domains.

*Parenting videos* will provide mothers with parenting skills education based on best practices in evidence-based positive parenting interventions (e.g., Parent Management Training, Positive Parenting) [42, 43]. To aid the transfer of DBT skills to the parenting context, the parenting skills videos will promote skills that align with the four core DBT modules (Mindfulness, Emotion Regulation, Distress Tolerance, and Interpersonal Effectiveness) to promote self-regulation in the parenting context and positive parent–child relationships.

*Weekly virtual group therap*y will provide the clinical team with the opportunity to consult with participants about their progress throughout the program. Participants can discuss video and worksheet content in these sessions with clinicians and other parents in the program during each session. The clinical team will consist of two Master’s or Ph.D. level clinical psychology trainees and a parent peer coach, a trained mother of young children who completed the BRIDGE program in the past.

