##### DBT only

Mothers in the DBT arm will not receive parenting skills training and will participate in 16 weeks of DBT skills training only led by two Master’s or Ph.D. level clinical psychology trainees. Participants in the DBT Skills condition will receive training following the DBT Skills Training Manual 2nd Edition [41] through weekly, synchronous 1.5-h virtual group therapy sessions, as well as worksheets to complete weekly. Mindfulness, Emotion Regulation, Distress Tolerance, and Interpersonal Effectiveness skill domains will be covered. Participants will also be instructed to complete weekly Diary Cards to track DBT skills use each week [40].

*Mood tracking* will be completed using a brief weekly survey including questions on depression, parenting stress, positive mood, and recent stressful experiences. Participants will be provided with a weekly score for their depressive symptoms and parenting stress. Participants will track and graph these weekly scores in the program handbook provided to them by the research team.

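### The primary model and the 75% power for BRIDGE vs DBT make no allowance for therapy-group clustering in the two active arms

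*Protocol article*

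**What the plan says.** All references are to the protocol article.

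- **Delivery.** Intervention description {11a} gives BRIDGE mothers "weekly synchronous 1-h virtual group therapy sessions" and DBT mothers "weekly, synchronous 1.5-h virtual group therapy sessions", each for 16 weeks. Two trainee clinicians lead each programme, joined in BRIDGE by a peer coach. SAU mothers receive a resource list and have no trial group.
- **Randomisation.** Individuals are randomised 1:1:1 in blocks. Sequence generation {16a} stratifies by "availability for virtual therapy timeslots (i.e., lunchtime or evening group) and (b) province of residence".
- **Primary analysis.** Statistical methods {20a}: "Linear models accounting for pre-intervention scores will be used as the primary analysis method". The analyses "will compare the changes over time between (a) the BRIDGE vs SAU groups and (b) BRIDGE vs DBT-only groups", each at "0.025 (combined type I error rate to 0.05").
- **Follow-up analysis.** The same section describes a linear mixed model "accounting for within-subject serial correlations and between-subject effects of the intervention and covariates". The covariates are not listed.
- **Sample size {14}.** For child symptoms: "60 per group will provide very high power (> 99%) to compare BRIDGE with SAU and adequate power (75"%) for BRIDGE against DBT, at d = 0.54. No ICC, group size or design effect is given.

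**The concern.** Mothers in one therapy group share clinicians, peers and 16 weeks of discussion, so their outcomes are likely to be correlated. This is a partially nested design: two arms are clustered by therapy group and the third is not. A model that treats all mothers as independent credits the active arms with more information than they carry.

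The effect is largest for BRIDGE vs DBT, where both arms are clustered. That comparison isolates what the parenting content adds, and it has the least stated power. If clustering is ignored, its confidence interval is too narrow, its test does not hold the 0.025 level, and the 75% is too high.

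**Working it through.** **Inputs from the protocol.** 60 per arm; d = 0.54 (BRIDGE vs DBT) and 1.08 (BRIDGE vs SAU) for child symptoms; d = 1.02 vs SAU for maternal depression; 0.025 per comparison. Sidedness is not stated.

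**Assumed inputs.** Group size m and ICC are not in the protocol. Trial status describes three rounds, and the strata name two time slots. If each arm ran one group per slot per round, there would be 3 × 2 = 6 groups per active arm, and 60 / 6 = 10 per group. The first round randomised 78, or 26 per arm, which would give 13 per group with two slots. The ICC is taken from 0.01 to 0.10. It means correlation specific to a therapy group; a round or time-slot effect common to both arms would cancel in BRIDGE vs DBT.

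**Step 1: reproduce the stated power.** With independent participants the noncentrality is 0.54 / √(2/60) = 2.958. A two-sided test at 0.025 on 118 degrees of freedom (df) gives 75.3% (76.3% by normal approximation). One-sided 0.025 or two-sided 0.05 gives 83–84%, and one-sided 0.05 about 90%. So 75% is the independence figure at two-sided 0.025, with no design effect.

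**Step 2: actual error of the unadjusted test.** Design effect DE = 1 + (m − 1) × ICC; the two-sided critical value is z = 2.241.

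- BRIDGE vs DBT, both arms clustered: error = 2 × [1 − Φ(2.241 / √DE)].
- BRIDGE vs SAU, one arm clustered: the same with (DE + 1) / 2 in place of DE.

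Example at m = 10, ICC 0.05: DE = 1 + 9 × 0.05 = 1.45. Then 2.241 / √1.45 = 1.861, giving 0.063. For SAU, (1.45 + 1) / 2 = 1.225 and 2.241 / √1.225 = 2.025, giving 0.043.

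**Step 3: power for BRIDGE vs DBT with the variance corrected.** Noncentrality = 0.54 / √(2 × DE / 60), first on 118 df (design effect alone), then on 2 × 6 − 2 = 10 df (a group-level t-test).

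| ICC (m = 10) | DE | Error, vs DBT | Error, vs SAU | Power, 118 df | Power, 10 df |
|---|---|---|---|---|---|
| 0 | 1.00 | 0.025 | 0.025 | 75% | 63% |
| 0.01 | 1.09 | 0.032 | 0.028 | 71% | 59% |
| 0.02 | 1.18 | 0.039 | 0.032 | 67% | 55% |
| 0.05 | 1.45 | 0.063 | 0.043 | 57% | 46% |
| 0.10 | 1.90 | 0.104 | 0.063 | 45% | 36% |

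Over m = 6 to 13 and the same ICCs, the error runs from 0.029 to 0.131 for BRIDGE vs DBT and from 0.027 to 0.076 for BRIDGE vs SAU. From the design effect alone, power against SAU stays above 98% throughout, for both d = 1.08 and d = 1.02.

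**Step 4: simulation of the baseline-adjusted linear model** (10,000 trials per setting, 60 per arm, 6 groups of 10 per clustered arm). At ICC 0.01 / 0.02 / 0.05 / 0.10 the error was 0.033 / 0.036 / 0.060 / 0.110 with both arms clustered and 0.029 / 0.031 / 0.041 / 0.063 with one. Adding stratum terms left these essentially unchanged.

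**Step 5: strata alone, no clustering.** With strata explaining 0 / 5 / 10 / 20% of residual variance, leaving them out gave an error of 0.023 / 0.022 / 0.019 / 0.011; including them gave 0.024–0.026. Omission makes the test conservative.

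**The case against.** The strongest reply is that this is a condensed article, that the primary model gets one sentence, and that an unseen analysis plan may add terms. This has force for covariates. The sentence does not say that the pre-intervention score is the only adjustment, the mixed model refers to unlisted covariates, and the section on concomitant care {11d} foresees further adjustment. It has less force for clustering. The article says which correlation its mixed model handles, and it publishes a power figure that holds only under independence. A later plan could repair the model, but not the 75% if the ICC is positive.

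Three stronger readings are tempting, and the documents do not support them:

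- *Leaving out the strata also makes standard errors too small.* The direction is the reverse (Step 5), and whether they are left out at all is inferred from silence.
- *The error rate certainly exceeds 0.025.* That is conditional on a positive ICC. The protocol gives neither ICC nor group size, and at ICC 0.01 with 10 per group the excess is mild (0.032 and 0.028).
- *Clustering alone cuts power to 55 / 46 / 36% at ICC 0.02 / 0.05 / 0.10.* Those figures come from a group-level test on 10 df, which has only 63% power even at ICC 0. About 12 of the lost points are due to the choice of test. The design effect alone gives 67 / 57 / 45%.

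**Conclusion.** The point holds for clustering. As stated, the primary model, the follow-up model and the BRIDGE vs DBT power make no allowance for therapy groups in the active arms. For any positive therapy-group ICC, standard errors are too small and each comparison exceeds its 0.025 level, BRIDGE vs DBT by more than BRIDGE vs SAU. How far depends on the assumed group size and ICC: the excess is small at ICC 0.01 and about fourfold for BRIDGE vs DBT at ICC 0.10 with 10 per group. The power problem is confined to BRIDGE vs DBT. It should be corrected before analysis, because it bears on a primary comparison and the correction is cheap.

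**What to change.** 1. Fit the T2 model with a random therapy-group effect in the BRIDGE and DBT arms only, treating SAU participants as singletons, with Satterthwaite or Kenward-Roger degrees of freedom. Put the same term in the follow-up mixed model.
2. Carry the therapy-group identifier into the analysis data. Clinicians already take attendance at sessions and the protocol says it is stored, so the identifier should be recoverable for the completed first round too.
3. State the expected group size and restate BRIDGE vs DBT power over a range of ICCs.
4. Separately, and of lesser weight: include time slot and province as covariates, for precision and to avoid a conservative test.

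Cost: analysis wording and one identifier. The intervals will be wider and the stated power lower. With about 12 active groups the group variance will be poorly estimated, and each group-level fixed effect added (round or time slot, for example) reduces the information on it further.
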